# 1. Abstract

The COVID-19 pandemic has caused significant morbidity and mortality across the world. Effective vaccines are now available but underutilized. In July 2021, Ascension Health implemented a mandate requiring all employees to obtain the COVID-19 vaccine by November 12th. In August 2021, the number of COVID-19 cases in the US increased rapidly, specifically in states with lower vaccination rates, many of which are served by Ascension Health facilities. In this study, we will evaluate a rapidly deployed health system initiative to use text messaging to nudge Ascension employees who have not yet been vaccinated to commit to a date and receive vaccination.

## 2. Overall objectives

To evaluate if using text messages to set a default date for COVID-19 vaccination can encourage higher and faster vaccination rates.

## 3. Aims

### 3.1 Primary outcome

The percent of participants that receive the COVID-19 vaccine within 2 weeks of the intervention.

### 3.2 Secondary outcome

Time to COVID-19 vaccination in days within 4 weeks of the intervention.

## 4. Background

The COVID-19 pandemic has caused significant morbidity and mortality across the world. Effective vaccines are now available but underutilized. In July 2021, Ascension Health implemented a mandate requiring all employees to obtain the COVID-19 vaccine by November 12th. In August 2021, the number of COVID-19 cases in the US increased rapidly, specifically in states with lower vaccination rates, many of which are served by Ascension Health facilities.

Nudges are subtle changes to the way information is framed or choices are offered that can have a significant impact on behavior. Status quo bias is a preference for the current state which is often used as a reference point when making decisions. Changes from the reference point are often faced with high inertia and this prevents changes in behavior. Default options are the setting of the baseline reference point and are often taken as an implicit recommendation.

In prior work, changing default options has led to significant changes in health-related behaviors. For example, changing prescription default settings in the EHR from opt-in to opt-out for generic prescriptions increased the rate of generic prescriptions from 75% to 98% across Penn Medicine (Patel et al. *Annals of IM*. 2014; Patel et al. *JGIM* 2018). Framing program participation as opt-out has led to a 22% increase in enrollment in a COVID-19 surveillance testing program (Oakes et al. *NEJM Catalyst* 2021) and triple enrollment in remote monitoring programs for medication adherence (Mehta et al. *JAMA Cardiology*. 2018) and diabetes management (Aysola et al. *AJHP* 2016)

## 5. Study Design

### 5.1 Design

This will be conducted as a two-arm randomized, controlled trial. The control arm will receive usual health system messaging about the importance and deadlines for receiving COVID-19 vaccination. The intervention arm will receive a text message stating that the vaccine is reserved for them on a specific date. They will have the ability to reschedule to a different day, opt-out of this text messaging intervention, or if previously vaccinated they can upload documentation to the Ascension website.

A list of Associates for whom Ascension does not have documentation of vaccination or exemption from vaccination will be provided by Human Resources at Ascension. Information on vaccine clinic locations and hours are available online and a link to them will be provided in the text message.

Participants sites will likely include Ascension Associates from the following markets: DC, Maryland, NY Binghamton, Kansas and/or Florida

The trial is anticipated to begin around: September 13, 2021.

### 5.2 Study duration

This rapid health system intervention will be completed within 1 month. We will follow participant vaccination status from the time the interventions were sent out until 2 weeks after the end of the first week of vaccination dates.

### 5.3 Target population

Ascension Associates for whom the health system does not have documentation of COVID-19 vaccine or exemption from vaccination

## 5.4 Accrual

The sample will be identified by the health system and there will not be active participant recruitment.

## 5.5 Key inclusion criteria

To be eligible, participants must be age 18 or older and an Ascension Associate without documentation of vaccination or exemption at the time of the intervention implementation

# 6. Participant recruitment

The sample will be identified by the health system and there will not be active participant recruitment.

# 7. Participant compensation

There will be no compensation to participants in this study.

# 8. Study procedures

## 8.1 Consent

A waiver of informed consent is requested for the following reasons. First, this is a rapid deployment of a health system initiative and it will not be feasible to consent each participant in a timely manner. Second, the health system has already implemented a mandate for COVID-19 vaccination for the target population. Third, if the control group was consented, it could change their behavior differently from what it would be under usual care and that could hinder evaluation of the effectiveness of the intervention. Fourth, we provide the opportunity for all intervention participants to opt-out of messaging if they would like to do that.

## 8.2 Procedures

Prior to the interventions, all Associates identified in the selected markets will be sent an email from Associate Health informing them of the upcoming text message intervention, that it will be staggered so some get it before others, and which phone number it will be sent from. Participants in the intervention arm will be sent up the following text messages (See Section 12.1 for full text message script).. Message 1 will inform them of Ascension's goal of keeping everyone safe during the pandemic, that a vaccine is reserved for them on a specific day, URL with vaccine clinic locations and times, and ability to either reschedule to another day, or obtain a link to upload documentation of vaccination. Message 2 will be sent the day before the scheduled date with vaccine clinic location and hours as well as allow them to reschedule, or

upload documentation if needed. Message 3 will be sent the morning of the date scheduled with vaccine clinic location and hours as well as allow them to reschedule, or upload documentation if needed. Message 4 will be sent the day after the date scheduled to ask if the vaccine was received or not. If yes, then the link for uploading documentation will be sent. If not they will be scheduled for another day and cycle back to Message 1. If the approach is found to be successful, participants in control will receive the same intervention about 2 weeks later.

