## 9. Analysis plan

Prior to analyses, we will produce data summaries to assess data quality, data distribution, and randomization success. All analyses will be evaluated using an intention-to-treat approach. An individual will be classified as vaccinated if they uploaded documentation of vaccination within 2 weeks after the end of the first week of vaccination appointments.

We estimate that a sample of 1450 (725 per arm) will provide at least 90% power to detect a 5 percentage point difference in vaccination between the intervention and control groups. This assumes a 20% vaccination rate in the control group and uses a two-sided alpha of 0.05.

The primary analysis will use a chi-square test to evaluate for differences in vaccination rate between the intervention and control group. Differences in time to vaccination will be evaluated using a t-test for means and Mann-Whitney test for medians. We will test the robustness of these findings by fitting a fully adjusted model with available participant characteristics. We will perform exploratory subgroup analyses for available participant characteristics.

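### The plan does not fix when controls are texted or how success is judged; on the natural reading, roll-out at about day 14 falls inside the 4-week secondary window and probably inside the Section 9 primary window

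*Combined protocol and SAP*

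**What the plan says.** Section 8.2 makes roll-out to controls conditional: "If the approach is found to be successful, participants in control will receive the same intervention about 2 weeks later". The same section says staff will be told in advance about the texting, and "that it will be staggered so some get it before others".

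The outcome windows are set in four places:

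- Section 3.1, primary: "The percent of participants that receive the COVID-19 vaccine within 2 weeks of the intervention".
- Section 9, classification: a person counts as vaccinated if they "uploaded documentation of vaccination within 2 weeks after the end of the first week of vaccination appointments".
- Section 5.2, follow-up: "from the time the interventions were sent out until 2 weeks after the end of the first week of vaccination dates". It adds: "This rapid health system intervention will be completed within 1 month".
- Section 3.2, secondary: "Time to COVID-19 vaccination in days within 4 weeks of the intervention".

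Section 9 applies intention-to-treat to every analysis and compares times with a t-test and a Mann-Whitney test. Sections 3, 5, 8 and 9 give no success criterion, no data cut-off before controls are texted, and no censoring of controls at that point.

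**The concern.** The trial compares texted with untexted employees, so the comparison is clean only while controls remain untexted. If controls are texted while outcomes are still accruing, intention-to-treat counts the vaccinations that follow as control events. Because roll-out depends on apparent success, the dilution arises when the texts seem to work.

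A short overlap is not automatically harmless. Section 9 classifies people by uploaded documents, and the first text in Section 12.1 invites those already vaccinated to upload. A text could therefore turn an undocumented but vaccinated control into an event the same day, with no new vaccination.

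The success call is a second difficulty. If roll-out comes at about day 14, someone must judge success by then, on data that Section 9 treats as incomplete and by a rule that is not stated.

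**Working it through.** **1. Calendar.** Inputs: anticipated start around 13 September 2021, a Monday (Section 5.1), taken as day 0; the Section 9 window, which is the end of the first appointment week plus 14 days; the 28-day secondary window (Section 3.2). Two assumptions are mine: messages go out on day 0, and reserved dates fall in that week or the next. The plan states no day count for the Section 9 window.

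| First appointment week ends | Window closes (+14) | Primary days after day 14 | Share of window |
|---|---|---|---|
| Fri 17 Sep, day 4 | day 18 | 18 − 14 = 4 | 22% |
| Sun 19 Sep, day 6 | day 20 | 6 | 30% |
| Fri 24 Sep, day 11 | day 25 | 11 | 44% |
| Sun 26 Sep, day 13 | day 27 | 13 | 48% |

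**2. Overlap under each possible anchor for the two weeks.**

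- *From launch (roll-out about day 14).* Section 9 primary: 4 to 13 days exposed. Section 3.1 primary: 14 − 14 = about 0 days. Secondary: 28 − 14 = 14 of 28 days, or 4 to 13 if follow-up really stops where Section 5.2 stops it (day 18 to 27).
- *From the end of the first appointment week (roll-out day 18 to 27).* Primary: about 0. Secondary: 28 − 27 = 1 to 28 − 18 = 10 days, or about 0 if follow-up stops as in Section 5.2.
- *From a success finding made when the Section 9 window closes.* Roll-out at 18 + 14 = day 32 to 27 + 14 = day 41. No overlap with either window.

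**3. The plan's own power figure.** Section 9 states 1450 in total (725 per arm), 20% against 25%, two-sided 0.05, at least 90% power. With the pooled-variance formula,

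power = Φ{ [ |p₁ − p₀|√n − 1.96√(2p̄(1 − p̄)) ] / √(p₀(1 − p₀) + p₁(1 − p₁)) },

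n = 725, p₀ = 0.20, p₁ = 0.25 and p̄ = 0.225:

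(1.346 − 1.157) / 0.589 = 0.320, so power = Φ(0.320) = 62.6%.

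The stated 90% is not reproduced; it needs 1464 per arm. That is a separate defect. It matters here only because it sets the baseline for the illustration.

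**4. Illustration of dilution.** Assumption, without a source in the plan: controls gain a fraction f of the 5-point effect before the window closes, and every trial crosses over. Then p₀ = 0.20 + 0.05f.

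| f | Control rate | Difference | Power, 725 per arm | Power, 1464 per arm |
|---|---|---|---|---|
| 0 | 20% | 5 points | 63% | 90% |
| 10% | 20.5% | 4.5 points | 53% | 83% |
| 25% | 21.25% | 3.75 points | 39% | 67% |
| 50% | 22.5% | 2.5 points | 20% | 36% |

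The last column separates dilution from the sample-size defect. In both columns the loss is smaller if crossover happens only after apparent success, because trials that do not trigger roll-out keep an untexted control arm.

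**The case against.** A reader might infer that the plan certainly contaminates its control arm. The documents do not support that. The anchor for the two weeks is not given. If the two weeks run from a success finding made after the Section 9 window closes, roll-out is at day 32 to 41 and nothing overlaps. The staggered wording favours the earlier reading, and the later one fits poorly with the one-month duration in Section 5.2 if that month includes control roll-out, but neither settles the matter. Roll-out is also conditional, so contamination is a risk and not a certainty.

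A reader might infer that the primary outcome is necessarily affected. Under Section 3.1 the window closes at day 14 and the overlap is about zero. The primary exposure exists only under Sections 5.2 and 9, and the conflict between these definitions is a problem in its own right. Section 3.1 does not rescue the success call, however: the window would close at about the moment controls are texted.

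A reader might take 39% or 20% as the trial's expected power. Those figures rest on unsourced control gains, assume that every trial crosses over, and start from a baseline lowered by a different error. With a 4-day overlap, a 50% gain would need very fast vaccination and upload.

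It is also fair to say that dilution of this kind would not by itself produce a false positive on the primary comparison. What stands is that nothing in the plan protects the control arm on the most natural reading.

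**Conclusion.** The concern holds as a gap in the plan with a probable, unquantified bias. The secondary overlap is the firmer part (confidence high to moderate). It does not depend on which primary definition governs: up to 14 of 28 days on the day-14 reading, or 4 to 13 if follow-up ends as Section 5.2 states. The primary overlap of 4 to 13 days holds with moderate confidence. It needs the day-14 reading, the Section 9 window, a launch on 13 September, and appointments in the same or next week.

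The expected direction is toward no effect when the intervention works. For time to vaccination this assumes that people not yet vaccinated stay in the comparison, as intention-to-treat implies; Section 9 does not say how they are handled. The documents do not allow the size to be estimated, and the power table is an illustration only.

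**What to change.** 1. Use one primary window in Sections 3.1, 5.2 and 9, and make follow-up long enough to cover the secondary window.
2. In Section 8.2, state what the two weeks are counted from and give a calendar date. State who judges success, on which data and by what rule.
3. Then choose one of two options:
   - **Hold roll-out.** Text controls only after the primary and 4-week windows have closed and the primary comparison has been run once.
   - **Cut follow-up.** In both arms, end the primary window and administratively censor time to vaccination on the day before control roll-out, counting only documents uploaded by then. Replace the t-test and Mann-Whitney comparison with a method that handles censoring, such as Kaplan-Meier curves with a log-rank test.

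**Cost.** Holding roll-out moves control texts from about day 14 to day 28 plus analysis time, a delay of about two weeks or more. The 12 November deadline is day 60 (17 days left in September + 31 + 12), so the time left after texting falls from 46 days to at most 32. Controls keep usual messaging meanwhile. Cutting follow-up costs no delay but shortens the outcome window and loses late uploads, so the 20% control rate assumed in Section 9 would need re-checking against the shorter window.

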## 9. Analysis plan

Prior to analyses, we will produce data summaries to assess data quality, data distribution, and randomization success. All analyses will be evaluated using an intention-to-treat approach. An individual will be classified as vaccinated if they uploaded documentation of vaccination within 2 weeks after the end of the first week of vaccination appointments.

We estimate that a sample of 1450 (725 per arm) will provide at least 90% power to detect a 5 percentage point difference in vaccination between the intervention and control groups. This assumes a 20% vaccination rate in the control group and uses a two-sided alpha of 0.05.

The primary analysis will use a chi-square test to evaluate for differences in vaccination rate between the intervention and control group. Differences in time to vaccination will be evaluated using a t-test for means and Mann-Whitney test for medians. We will test the robustness of these findings by fitting a fully adjusted model with available participant characteristics. We will perform exploratory subgroup analyses for available participant characteristics.

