# 12. Appendix

## 12.1 Text messaging script

### **Initial Text at 9am market time**

[First name Last name], Ascension is committed to providing a safe environment for associates, patients and visitors. All associates are required to receive the COVID-19 vaccine series by November 12, 2021. A dose is reserved for you on [insert day of the week or date, e.g. Monday, August 30, 2021].

Vaccine clinic locations and hours can be found here: [insert Market specific URL]

Reply Reschedule if you need to select a different date. Reply Upload if already vaccinated and you need to upload your vaccine card.

- If Reschedule: What day works best for you? Reply Monday, Tuesday, Wednesday, Thursday, or Friday.
  - You are confirmed for [insert day selected and reset appointment date in system]
  - If Other: Sorry, we did not recognize that response. You can text back Monday, Tuesday, Wednesday, Thursday, or Friday.
- If Upload: Submit your vaccination verification here; you will need your employee ID number and a photo of your vaccine documentation:  
<https://gdaintranet.ascension.org/home/covid-19-vaccine-external-documentation> [then stop text messages]
- If Other: Sorry, we did not recognize that response. You can text back Reschedule or Upload. If that day works for you, then you can visit any clinic within the hours they are open on that day. You may also receive vaccination from another site and Upload your vaccine care. If questions, email: [[contact]](mailto:[contact])

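### The primary outcome is scored by uploaded documentation with no stated dose-date condition, and the only upload prompts described are in the intervention texts, so old vaccinations can count as intervention successes

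*Combined protocol and SAP*

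**What the plan says.** Section 3.1 gives the primary outcome as "The percent of participants that receive the COVID-19 vaccine within 2 weeks of the intervention". Section 9 turns this into a scoring rule under which an individual is "classified as vaccinated if they uploaded documentation of vaccination within 2 weeks after the end of the first week of vaccination appointments". The rule does not mention the date on the card.

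The target population in section 5.3 is "Ascension Associates for whom the health system does not have documentation of COVID-19 vaccine or exemption from vaccination", and section 5.5 likewise asks for "an Ascension Associate without documentation of vaccination or exemption at the time of the intervention implementation". Entry therefore depends on the record, not on vaccination status. The plan expects some participants to be vaccinated already: section 5.1 says of the intervention arm that "if previously vaccinated they can upload documentation to the Ascension website".

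In the section 12.1 script, the first text says "Reply Upload if already vaccinated and you need to upload your vaccine card". The day-before and same-day texts carry an equivalent invitation, and replying Upload returns the link. The day-after text asks people who say they were vaccinated to send a card only if the dose was given somewhere other than Associate Health. Section 8.2, by contrast, describes the link going to everyone who answers yes.

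For controls, section 5.1 says: "The control arm will receive usual health system messaging about the importance and deadlines for receiving COVID-19 vaccination". The advance email to all Associates in section 8.2 is described as covering the coming texts, their staggering and the sending number. Uploading is not mentioned.

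**The concern.** The randomised treatment can change the chance that the endpoint is recorded, separately from any effect on vaccination. An Associate vaccinated before the trial who sends in an old card after a text meets the section 9 rule. The same Associate in the control arm, with no described prompt, is less likely to do so.

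Randomisation balances the share of such people between arms but not their uploading afterwards. Intention-to-treat analysis and the planned covariate-adjusted model do not remove the difference, because it arises after randomisation and through the treatment itself.

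At stake is the meaning of a positive result. A significant chi-square test could reflect more vaccination, more complete paperwork, or both, and the plan as written would not separate them.

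**Working it through.** **The plan's own figure.** Section 9 gives 725 per arm, 20% against 25%, two-sided alpha 0.05, chi-square test, and at least 90% power. With mean rate 0.225, the null standard error is sqrt(2 x 0.225 x 0.775 / 725) = 0.0219, so the significance threshold is 1.96 x 0.0219 = 0.043. Power is Phi((0.050 - 0.043) / 0.0219), which is 62.6% unrounded. The stated 90% does not reproduce; 1450 in each arm would give 89.7%. That is a separate matter. It is shown here because the same formula is used below.

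**Main route: old cards.** Let q be the share of those randomised who are already vaccinated but undocumented, and uI and uC their probabilities of uploading by the cut-off in each arm. With no effect on vaccination, the expected difference is

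b = q x (uI - uC).

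None of q, uI or uC is in the documents, so all values below are assumptions. Each row takes a recorded control rate of 20%, an intervention rate of 20% + b, and 725 per arm.

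| q | uI - uC (points) | b (points) | Two-sided rejection |
|---|---|---|---|
| 5% | 10 | 0.5 | 5.6% |
| 10% | 20 | 2.0 | 15.4% |
| 20% | 20 | 4.0 | 45.2% |
| 20% | 25 | 5.0 | 62.6% |
| 20% | 30 | 6.0 | 77.5% |

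The first row is close to the nominal 5%. The fourth reproduces the plan's whole 5-point target effect without one extra vaccination.

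**Secondary route: timing of uploads for new doses.** Suppose the true rate is 20% in both arms, and 20% of control doses but 5% of intervention doses are uploaded after the cut-off (assumed). The recorded rates are 0.20 x 0.80 = 16% and 0.20 x 0.95 = 19%, a 3-point difference. This applies late uploading to every dose. If Associate Health doses are recorded directly, only doses given elsewhere depend on a card. The 3 points then shrink to 3 x (share of doses given elsewhere), taking that share as equal in the two arms.

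**A possible offset.** If section 9 is read literally and only uploads count, an Associate Health dose that is never uploaded scores as a failure. The day-after script does not ask those people for a card. If the texts bring more intervention participants to Associate Health clinics, this error would work against the intervention. The documents give no figure from which to size it.

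**The case against.** The strongest reply is that section 9 can be read differently. Its time phrase may govern the vaccination and not the upload. Section 3.1 speaks of receiving the vaccine, section 5.2 follows vaccination status from the sending of the interventions, and the secondary outcome is time to vaccination in days, which implies that dose dates will be available. This stands in part: the authors may have intended a dose-date rule. But section 9 does not state one, and nothing in the plan says how a card dated before launch is to be scored.

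Three stronger conclusions are tempting and not supported:

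- A reader might infer that controls receive no upload prompt at all. The content of their usual messaging is not reproduced, and the mandate gives them some reason to document. The documents show only that no such prompt is described.
- A reader might infer that the total error must favour the intervention. That direction follows for old cards if the texts raise uploading. The late-upload route is limited by the day-after script, and missed Associate Health doses could partly offset the bias.
- A reader might infer that the trial would mainly measure paperwork. With small inputs, such as 5% and 10 points, the distortion is slight. Nothing in the documents places the trial at either end of the range.

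**Conclusion.** The concern holds in this form. As written, the section 9 rule does not exclude vaccinations given before launch, the eligible population can include people with such vaccinations, and the only upload prompts the documents describe are in the intervention texts. Old cards uploaded because of those prompts would bias the primary comparison toward the intervention by q x (uI - uC).

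The size cannot be determined from the documents. It rests on the two assumed inputs, on the plan's 20% control rate and on 725 per arm. Faster uploading of new doses is a secondary contributor, limited to doses not recorded directly. The net direction across all routes is likely but not established. Because this is the primary endpoint and the correction is mostly wording, the rule should be settled before analysis.

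**What to change.** Rewrite the scoring rule in section 9, identically for both arms:

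- **Event.** A first COVID-19 vaccine dose dated on or after a common launch date and by the end of one stated window. Specifying the first dose matters because the script refers to a vaccine series, and a second dose after launch should not turn a pre-trial vaccination into an event.
- **Window.** Reconcile section 3.1, which counts two weeks from the intervention, with sections 5.2 and 9, which run to two weeks after the first week of appointments. Close the window before any control participant is texted; section 8.2 puts that about two weeks later.
- **Source.** Take the dose date from an uploaded card or from Associate Health records, and reconcile section 8.2 with the day-after script on who is asked for a card.
- **Pre-launch first doses.** Count them as non-events and keep these people in the denominator. Excluding them would remove more from the intervention arm, where prompting makes them easier to find.
- **Data pull.** Use one common later extraction for both arms, so that doses given in the window but uploaded late are counted. A provisional readout can still inform the control rollout.
- **Process outcomes.** Report by arm the upload rate and the number of uploads showing a pre-launch dose.

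The cost is revised wording, extraction of dose dates (possibly from card images) and a final readout later than the one-month schedule in section 5.2. Documentation may still be incomplete at the later pull: the 12 November date is a deadline for vaccination, exemptions exist, and the plan does not say that records will be complete by then.

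### The primary endpoint has two incompatible definitions, and the undefined timing of control texting may place it inside the follow-up window

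*Combined protocol and SAP*

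**What the plan says.** Section 3.1 gives the primary outcome as "The percent of participants that receive the COVID-19 vaccine within 2 weeks of the intervention". Section 9 classifies an individual as vaccinated if their documentation was uploaded "within 2 weeks after the end of the first week of vaccination appointments". Section 5.2 follows vaccination status "until 2 weeks after the end of the first week of vaccination dates", which is the Section 9 closing point. The secondary outcome in Section 3.2 is "Time to COVID-19 vaccination in days within 4 weeks of the intervention".

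On the control arm, Section 8.2 says: "If the approach is found to be successful", then "participants in control will receive the same intervention about 2 weeks later". It does not say what the 2 weeks are counted from, what counts as success, or when success is judged. Section 9 applies intention-to-treat to all analyses, and no section excludes or censors a control's outcome after that control has been texted. On the calendar, Section 5.1 says only: "The trial is anticipated to begin around: September 13, 2021".

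**The concern.** The two statements of the primary endpoint differ in three ways: when the clock starts, when it stops, and what counts as the event (a dose received, or a document uploaded). Some people are therefore vaccinated under one and not under the other:

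- A dose after day 14, uploaded before the Section 9 window closes, counts only under Section 9.
- A dose before day 14 whose card is uploaded after the Section 9 window closes counts only under Section 3.1.

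The first group matters for the estimated effect because the texting script in Section 12.1 creates it. Intervention participants who reschedule from the day-before or same-day text are offered a day in the following week. Those who answer No on the day after the appointment are reserved for the next Monday. How much of this second cycle is counted depends on which window is used.

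No section says which definition prevails, so the window and the event could be chosen after the results are known.

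The second issue is whether controls could be texted while their outcomes are still being counted. If so, intention-to-treat would keep them in the control arm and the difference would be pulled toward zero.

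**Working it through.** The documents give no day count for the Section 9 window, so there is no stated figure to reproduce. The length has to be derived.

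**Inputs.** Day 0 is the date of Message 1. The start is around 13 September 2021, a Monday (Section 5.1). Appointments are Monday to Friday (Section 12.1). Message 2 goes out the day before the appointment (Section 8.2), so appointments follow Message 1. Assumed, because not stated: the weekday of Message 1, whether the first appointments fall in the same week or the next, and whether a week ends on Friday or Sunday.

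**Closing day of the Section 9 window.** W = E + 14, where E is the day on which the first appointment week ends.

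- Monday send, same-week appointments, Friday end: E = 4 (17 September), so W = 18 (1 October).
- Monday send, next-week appointments, Friday end: E = 11 (24 September), so W = 25 (8 October).
- Sends on Monday to Wednesday, week ending Friday or Sunday: the shortest case is a Wednesday send, same week, Friday end, 2 + 14 = 16. The longest is a Monday send, next week, Sunday end, 13 + 14 = 27.
- A Thursday send for Friday appointments gives 1 + 14 = 15. W = 14 would require the appointment week to end on the day Message 1 is sent, which does not fit the message sequence.

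So the Section 9 window closes later than day 14 in every workable case.

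**Who moves between windows.** In the next-week case, first appointments fall on days 7 to 11 and appointments moved to the following week on days 14 to 18. Only the Monday, day 14, is inside a 14-day window. All five days are inside a window closing on day 25. In the same-week case, moved appointments fall on days 7 to 11 and are inside both windows.

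**Overlap with control texting.** Overlap = closing day minus the day controls are texted, or zero if negative. The secondary window closes on day 28. Each cell gives the W = 18 case, then the W = 25 case.

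| '2 weeks later' counted from | Controls texted on day | Overlap, Section 9 window | Overlap, secondary window |
|---|---|---|---|
| First intervention text | 14; 14 | 18 − 14 = 4; 25 − 14 = 11 | 28 − 14 = 14; 14 |
| End of first appointment week | 4 + 14 = 18; 11 + 14 = 25 | 0; 0 | 28 − 18 = 10; 28 − 25 = 3 |
| A success decision made when the Section 9 window closes | 18 + 14 = 32; 25 + 14 = 39 | 0; 0 | 0; 0 |

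A 14-day primary window has no overlap in any row. In all the calendars above, follow-up under Section 5.2 also ends before day 28, so it does not cover the whole secondary window.

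**The case against.** A reader might infer that contamination of the control arm is built into the design. The documents do not support that. Texting of controls is conditional on success, and the 2 weeks have no stated origin. The advance email in Section 8.2 describes a staggered rollout but sets no date. Two of the three readings above leave the Section 9 window clear. Even on the day-14 reading, overlap days overstate exposure: with next-week appointments, a control texted on day 14 has no reserved date before day 21, so 7 of the 11 days precede any control appointment. Any contamination would shrink the difference, not manufacture a benefit. All of this stands.

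A reader might also infer a specific loss of power. If controls realised a share f of the planned 5-point effect, the difference would be 5 × (1 − f) points. The documents give no basis for f, which could lie anywhere from 0 to 1, so no power figure is warranted. Nor do the documents state an 18 or 25 day window; those counts are derived under stated assumptions.

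Finally, Sections 5.2 and 9 share a closing point and Section 3.1 is the outlier, so the longer window may be the one intended. That is a fair guess, but no text makes it the rule. It would also leave receipt against upload unresolved, because Section 3.1 counts doses and Section 9 counts documents.

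**Conclusion.** The contradiction in the primary endpoint is established from the text and needs no assumption. Section 3.1 conflicts with Section 9 on clock and event, and with Section 5.2 on the closing point. The windows would coincide only if the intervention in Section 3.1 meant the end of the first appointment week, which no section says. The gap beyond day 14 is 4 or 11 days for a Monday send with a Friday week end, and about 2 to 13 days on the wider range of calendars. This must be resolved before outcome data are examined.

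The overlap with control texting is a risk the plan leaves open, not an established fact. It affects the Section 9 window if the 2 weeks run from the first intervention text. It affects the 4-week secondary window on that reading, and also if they run from the end of the first appointment week. The direction would be toward zero; the size is unknown.

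**What to change.** 1. Use one primary definition in Sections 3.1, 5.2 and 9. Set day 0 as the calendar date on which Message 1 is sent in that market, applied to both arms, since controls have no Message 1 of their own at that point. State a single closing day. Define the event by dose date within the window, and allow the card to be uploaded later.
2. Choose either 14 days or the longer Section 9 window, expressed as a day number. Either is acceptable if fixed before the data are seen.
3. In Section 8.2, state that control texting starts only after the primary window closes. Alternatively, state in Section 9 that no between-arm analysis uses control outcomes after a control's first intervention text.
4. Apply the same rule to the 4-week secondary outcome, and align the end of follow-up in Section 5.2 with it.

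The cost is mainly wording, but each choice has a price. A 14-day window yields fewer events and may cut off rescheduled appointments, which are part of the intervention. A longer window delays texting of controls if texting has to wait for it to close. If controls are texted before day 28, the between-arm follow-up for the secondary outcome may have to be shortened.
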